## Methods/Design

### Approach to research questions

The primary outcomes of this trial are the assessment of cardiovascular (changes in , plasma albumin content and plasma volume) and intramuscular (selected genes and proteins involved in cellular adaptive processes) training-induced adaptations, and whether protein co-ingestion (immediate or overnight) improves the magnitude of these adaptations. In accordance, two phases of testing will be conducted.

Phase I will be addressed by evaluating a carbohydrate-protein mixture against an energy-matched carbohydrate control to examine the influence of post-exercise protein intake in enhancing endurance training adaptations. Participants in Phase I will be randomly allocated to a group receiving an isocaloric carbohydrate supplement or a group receiving a carbohydrate-protein supplement, in a randomized investigator-participant double-blind manner, whereby the chief investigator ([name]) and participants will be blinded from the trial allocation. The acute post-exercise phase is important when considering the metabolic priority for recovery to be initiated [3, 21] and the potentiated sensitivity to nutritional interventions during this period [22]. It has been established that glycogen resynthesis and amino acid uptake rates are augmented following an exercise bout, and that the ingestion of carbohydrate and protein stimulate this process [6, 23–25]. This has subsequently prompted large numbers of studies to investigate the role of combined carbohydrate-protein ingestion in restoring glycogen stores, potential attenuation of decrements of skeletal muscle functional integrity and subsequent exercise performance [12, 26]. It is now generally accepted that incorporating protein into a post-exercise feeding regimen is a viable strategy to enhance recovery, mainly through observations in acute based studies [7, 8, 21, 27–33]. Yet, the effects of protein ingestion are more likely to be realized beyond the acute recovery phase, given that upregulation of endurance exercise-specific gene expression peaks between 10 and 24 hours following an exercise bout, and may surpass 96 hours for muscular recovery and adaptive remodeling to occur, suggesting that repeated bouts of exercise are required to detect worthwhile training adaptations [3, 34].

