#### Muscle biopsy sampling

An 80 to 100 mg muscle biopsy sample will be obtained at baseline and follow-up via needle biopsy techniques [57]. A 5 mm skin incision will be made from the lateral portion (vastus lateralis) of the thigh from the same leg at baseline and follow-up and separated by 2 to 3 cm, with the use of dominant and non-dominant legs being counterbalanced between participants. The detailed procedures for obtaining the muscle biopsy samples are reported elsewhere [47].

Once removed from the thigh, each muscle sample will be immediately immersed in liquid nitrogen and kept stored pending subsequent analysis. The obtained muscle samples will be freeze-dried and dissected free of any visible adipose, blood and connective tissue, and separated into two specimens with a scalpel. One part of the frozen muscle tissue will be used to evaluate the impact of endurance training on selected genes and proteins involved in cellular adaptive processes (such as *GLUT-4, HKII, FABPpm, PDK4, PPARδ, PGC-1α, SIRT1, AMPK, P38MAPK, P53, ERK1* and *2*) using quantitative real-time PCR and Western blotting, as previously described [58]. Another part of the frozen muscle tissue will be utilized to determine the enzyme activity of citrate synthase [59].

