### Data analysis

The majority of data include measurements of cardiovascular and intramuscular markers of endurance training adaptations at baseline and follow-up, and thus treatments × time interactions will be explored using a general linear model with baseline included as a covariate, to account for any baseline imbalances because of regression to the mean [62]. The majority of variables in this experiment therefore involve a single comparison between two level scores, and so will not be adjusted for multiple comparisons across the different variables. Any data that require a single comparison of two means will be tested for normality using the Shapiro-Wilk test before using an independent t-test or non-parametric equivalent to examine differences between treatment arms (for example, magnitude of change in absolute and relative  between treatments). Relationships between outcome variables will be examined using a Pearson’s product-moment correlation and any meaningful associations (r ≥0.7) between baseline, and the magnitude of response to exercise training will be further explored by post-stratification of the treatment group according to baseline status. Significance will be set at ≤0.05 and all results being reported as the mean and standard error of the mean (SEM) unless stated otherwise.

Participants will be advised at the initial trial enrollment meeting to carefully consider the required investment of time and effort involved in the current project. This will be undertaken to minimize any negative impact associated with loss to follow-up, and consequently likely withdrawal can be made prior to randomization [63]. However, any unforeseen circumstances or withdrawal resulting in loss to follow-up will be documented and reported in the final trial report. In accordance, the handling of missing data subsequent to withdrawal will be primarily approached in a complete-case analysis adjustment method, while an imputation method will be considered where appropriate [64, 65].

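### Three cardiovascular outcomes and a panel of 11 to 12 genes and proteins are all primary, each tested at 0.05, and the reason given for not adjusting covers multiplicity only within a variable

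*Protocol article*

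**What the plan says.** Under Approach to research questions, the protocol article opens its list of outcomes with "The primary outcomes of this trial are the assessment of cardiovascular (changes in" and continues with "plasma albumin content and plasma volume) and intramuscular (selected genes and proteins involved in cellular adaptive processes) training-induced adaptations". The symbol after the opening words was lost in text extraction; I read it as maximal oxygen uptake, which the Background discusses together with plasma volume and albumin. No outcome is ranked above another, and the same list serves both phases.

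Muscle biopsy sampling gives examples of the panel: "GLUT-4, HKII, FABPpm, PDK4, PPARδ, PGC-1α, SIRT1, AMPK, P38MAPK, P53, ERK1* and *2". They are to be measured "using quantitative real-time PCR and Western blotting". Citrate synthase activity is to be measured on a separate part of the specimen.

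Data analysis then gives its premise: "The majority of variables in this experiment therefore involve a single comparison between two level scores". From that premise it draws the rule that the variables are left unadjusted: "and so will not be adjusted for multiple comparisons across the different variables". It adds: "Significance will be set at ≤0.05".

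The Background ends with one hypothesis per phase. Phase I expects a benefit of protein on cardiovascular but not on intramuscular adaptation. Phase II expects overnight feeding to improve markers of mitochondrial biogenesis.

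**The concern.** The argument in Data analysis does not reach its conclusion. A single two-arm comparison per variable means that no post-hoc correction is needed among arms. It says nothing about how often chance alone yields a significant result when many variables are tested, and the clause that rules out adjustment is explicitly about the different variables.

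This is not a detail left for an analysis plan. The article settles the question and gives a reason, so an analysis plan that adjusted across variables would contradict it.

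What is at stake is how much weight a finding labelled primary can carry. In Phase I, a chance result on a muscle marker would be reported as a primary finding against the trial's own hypothesis. In Phase II, the hypothesis refers to a class of markers and names none, so several panel members could be offered as support.

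**Working it through.** **Plan's own figure.** The article states no familywise error rate. The only related calculation is the sample size: 24 participants, 90% power, two-sided t-test at 0.05, difference 5.3 and SD 3.3 ml/kg (d = 5.3/3.3 = 1.606), again read as maximal oxygen uptake. With the noncentral t distribution, 12 per arm gives 96.4% power, and 90% is already passed at 10 per arm (92.4%). So 24 is more than enough for one test at 0.05. The sizing makes no allowance for other primary outcomes.

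**Number of primary tests, k.**
- Cardiovascular: 3 (Approach to research questions).
- Markers named: 11 if ERK1 and ERK2 count as one, 12 if as two (Muscle biopsy sampling).
- Total: 3 + 11 = 14 or 3 + 12 = 15 per phase.

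**Independent tests, no true effect.** Chance of at least one p ≤ 0.05 is 1 − 0.95^k:
- k = 14: 1 − 0.95^14 = 0.512
- k = 15: 1 − 0.95^15 = 0.537
- k = 3: 1 − 0.95^3 = 0.143
- k = 11: 1 − 0.95^11 = 0.431
- k = 12: 1 − 0.95^12 = 0.460

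**Correlated tests.** The documents give no correlations, so a range is assumed. Normal test statistics with a common pairwise correlation were simulated and tested two-sided at 0.05:

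| Set | k | Independent | Correlation 0.3 | Correlation 0.5 |
|---|---|---|---|---|
| Cardiovascular | 3 | 14% | 14% | 13% |
| Markers | 11 to 12 | 43 to 46% | 37 to 40% | 30 to 32% |
| All primary | 14 to 15 | 51 to 54% | 44 to 46% | 35 to 36% |

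At an extreme correlation of 0.9, the figure for all 14 to 15 is about 14%. Using t statistics with 13 per arm instead moves the results by no more than about two points.

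**If every marker were tested as both mRNA and protein (assumption).** The count becomes 3 + 22 = 25 or 3 + 24 = 27, and the chance is 72 to 75% if independent and 47 to 48% at correlation 0.5.

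**Cost of adjusting over everything.** Bonferroni gives 0.05/14 = 0.0036 or 0.05/15 = 0.0033 per test. With the protocol's own difference and SD, power for maximal oxygen uptake is then 74% or 73% at 12 per arm, and about 90% at 16 per arm. With maximal oxygen uptake as the only primary outcome, the level stays at 0.05 and the sample size does not change.

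**The case against.** Several objections stand and limit the point.

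- **Independence is unlikely.** Blood sampling says that plasma albumin content is calculated from the change in plasma volume, so two of the three cardiovascular outcomes are linked by construction, and the markers may well be correlated too. A reader might infer that a false-positive primary finding is as likely as not. That holds only for independent outcomes with every null true.
- **No rule says that any one significant outcome makes a phase positive.** A reader might infer one, but Data analysis speaks only of exploring interactions, and the hypotheses are set by domain. A chance marker result in Phase I would contradict its hypothesis. The set that could falsely confirm Phase I is the three cardiovascular outcomes, about 14%, and about half that in the predicted direction. This narrows the point but does not remove it, because a chance marker result would still be a false claim on an outcome labelled primary.
- **Phase II does not rest wholly on the panel.** Citrate synthase activity is measured outside it.
- **The larger count is not stated.** The article names two assay methods but does not say that every marker is tested by both.
- **The list of examples is not a fault in itself.** A condensed article may abbreviate a list that is closed in the full protocol.

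It can also be said that the non-adjustment is openly declared, so readers can discount isolated marker results. That is true, but it does not repair a rationale that answers a different question.

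**Conclusion.** The point holds: the article fixes several unranked primary outcomes at 0.05 each and rules out adjustment for a reason that applies only within a variable. With no true effect, the chance of at least one false-positive primary result per phase is about 35 to 54% for 14 to 15 outcomes with correlation between 0.5 and 0. By domain it is 13 to 14% for the cardiovascular outcomes and 30 to 46% for the markers over the same range. All of these exceed 5%. They assume two-sided tests at 0.05, equal correlations and the count of named markers. They would be higher if markers are tested as both mRNA and protein. The documents do not support a flat statement of even odds or of a win on any single marker.

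**What to change.** - **Phase I:** name maximal oxygen uptake as the single primary outcome, tested at 0.05.
- **Phase II:** have the investigators name one primary outcome for mitochondrial biogenesis before recruitment to that phase starts. Citrate synthase activity is one candidate because it is already measured, but the choice is theirs. It is not among the listed primary outcomes and the sample size was not derived for it, so they should state what difference the planned 32 participants could detect.
- **Plasma volume and plasma albumin content:** make them secondary, with Holm's procedure.
- **Gene and protein panel:** control the false discovery rate across it (Benjamini-Hochberg), or label it exploratory.
- **Data analysis:** delete the sentence that justifies non-adjustment.

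For Phase I, neither the significance level nor the sample size changes. The cost is that single-marker results carry less weight. Because Phase I has been randomizing since 11 December 2013 and the trial is registered, the change of primary outcomes must be recorded as an amendment before unblinding, and the registration brought into line. Phase II recruitment had not begun when the article was written, so the change is easier there.

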Cardiovascular adaptations are a hallmark of endurance exercise training. An enhancement in oxidative capacity and maximal oxygen uptake () in response to aerobic training with post-exercise protein ingestion has been observed by some [10, 11], but not all [20] studies. In concordance, the role of protein feeding in enhancing the adaptive response to endurance training may not reside in the intramuscular milieu. Rather, noticeable cardiovascular improvements in  via an increase in plasma volume and plasma albumin content have been shown with protein ingestion [10, 11]. However, the addition of other nutrients such as caffeine, flavonoids, multivitamins and ribose [11, 20], in addition to the absence of macronutrient-specific comparisons by not including a carbohydrate-only supplement [10], makes it difficult to conclude whether these improvements in training adaptation are a result of protein intake *per se*. Interestingly, the magnitude of improvement in  during endurance training was greater when whey protein was ingested relative to a placebo [10], or when milk-based protein available in the form of chocolate milk was co-ingested, when compared to an energy-matched carbohydrate supplement and a placebo [11]. Collectively, these findings may infer nutrient-specific effects of post-exercise supplementation on endurance training adaptations.

In summary, recent scientific evidence from acute laboratory investigations and relatively extended cycling-based training studies supports the notion that nutrient intake can increase protein accretion and, ultimately, this may influence the magnitude of the training effect. This nutrient-exercise interaction may modulate the adaptive response to training and protein feeding appears to be an important factor in mediating this process. However, examining the long-term outcomes of these acute mechanistic models, particularly during free living endurance-type exercise, require further investigation. This project aims to address two issues (Phase I and Phase II). Phase I will address whether protein co-ingestion with carbohydrate immediately following exercise can increase the magnitude of cardiovascular and intramuscular training adaptations to endurance training when compared with ingestion of carbohydrate alone. Phase II while address to what extent the timing of protein co-ingestion (overnight versus immediate feeding) impacts upon those training adaptations.

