### Sample size estimation

*A priori* sample size estimation (G*power version 3.1.7, University Düsseldorf, Düsseldorf, Germany) from data in the literature similar to the proposed work [11], revealed that a total of 24 participants are required to achieve 90% power to detect a worthwhile increase in an endurance performance () of 5.3 ml · kg^−1^ and standard deviation of 3.3 ml · kg^−1^, using a two-tailed t-test for independent means with an alpha level of 0.05. Rolling recruitment of 32 participants in each phase of testing will therefore be conducted when considering an anticipated 15% dropout rate [11, 36].

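### Two analyses cover the change in maximal oxygen uptake, one adjusted for baseline and one a normality-gated test on raw change, and the plan does not say which decides

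*Protocol article*

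**What the plan says.** The Data analysis section of the protocol article gives two rules in one paragraph.

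- **Baseline-adjusted model.** Its scope is wide: "The majority of data include measurements of cardiovascular and intramuscular markers of endurance training adaptations at baseline and follow-up". For these data, "treatments × time interactions will be explored using a general linear model with baseline included as a covariate", and the stated reason is baseline imbalance and regression to the mean.
- **Gated test.** Data that call for one two-group comparison of means are to be "tested for normality using the Shapiro-Wilk test before using an independent t-test or non-parametric equivalent to examine differences between treatment arms". The illustration is "for example, magnitude of change in absolute and relative", followed by a symbol that was lost when the text was extracted from the PDF.

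The lost symbol is read here as maximal oxygen uptake. That is an inference, but a firm one. The Background spells the quantity out at its first use ("An enhancement in oxidative capacity and maximal oxygen uptake") and the symbol is missing after it. The section on submaximal and maximal oxygen uptake measurements shows the same gaps. Approach to research questions opens its list of primary outcomes with the same missing symbol: "The primary outcomes of this trial are the assessment of cardiovascular (changes in".

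Sample size estimation sizes each phase on this outcome with an independent t-test, for a difference "of 5.3 ml · kg^−1^ and standard deviation of 3.3 ml · kg^−1".

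**The concern.** Maximal oxygen uptake is measured at baseline and follow-up, so it falls under the first rule. Its change between arms is the named example of the second. Nothing says which result carries the conclusion.

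The two rules do not answer different questions. If change is regressed on arm and baseline, the arm coefficient is the same as when follow-up is regressed on arm and baseline. Under randomisation, the t-test on change and the adjusted model therefore estimate the same treatment effect, and their p-values compete for one claim.

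Three things are at stake. The choice of decisive result can be made after both are seen. The outcome used for sizing is steered to the analysis that leaves out the adjustment the paragraph argues for. And with 12 to 16 participants per arm, a normality test with little power decides whether means or ranks are compared, while the rank test has no place for baseline or sex.

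**Working it through.** **Inputs from the protocol article.** Difference 5.3 and SD 3.3 ml/kg (units as printed), two-sided alpha 0.05, 24 evaluable participants for 90% power, 32 recruited per phase, 15% dropout, two arms per phase.

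**Assumptions, because the article does not give them.** Allocation is 1:1. The SD of 3.3 is that of the change. Variances are equal at the two times. The baseline to follow-up correlation rho is taken from 0.5 to 0.9. Shapiro-Wilk is applied in each arm at 0.05, with a switch to Mann-Whitney if either arm fails. Data are normal.

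**Stated sample size.** The standardised difference is 5.3/3.3 = 1.606. The exact noncentral-t calculation gives 10 per arm, 20 in total, with 92.4% power. The stated 24 gives 96.4%, so the figure of 24 at 90% is not reproduced. That is a separate matter, and nothing below depends on it.

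**Precision.** In large samples, Var(adjusted)/Var(change) = (1 − rho²)/[2(1 − rho)] = (1 + rho)/2. Estimating the baseline slope multiplies this by about 1 + 1/(N − 4). After 15% dropout 32 × 0.85 = 27.2 remain, about 13 per arm. With N = 26 the factor is 1 + 1/22 = 1.045.

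**Conditional bias of the change score.** Given a chance baseline imbalance, the raw change comparison is off by (1 − rho) times that imbalance, in the opposite direction. The imbalance has SD √(2/13) = 0.392 baseline SD. To convert to ml/kg, the baseline SD is 3.3/√[2(1 − rho)].

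| rho | (1 + rho)/2 | × 1.045 | SD of bias, baseline SD units | SD of bias, ml/kg |
|---|---|---|---|---|
| 0.5 | 0.75 | 0.78 | 0.5 × 0.392 = 0.20 | 0.196 × 3.30 = 0.65 |
| 0.7 | 0.85 | 0.89 | 0.3 × 0.392 = 0.12 | 0.118 × 4.26 = 0.50 |
| 0.8 | 0.90 | 0.94 | 0.2 × 0.392 = 0.08 | 0.078 × 5.22 = 0.41 |
| 0.9 | 0.95 | 0.99 | 0.1 × 0.392 = 0.04 | 0.039 × 7.38 = 0.29 |

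**Simulation of both routes.** It used 12 per arm (the stated 24), with 20,000 runs under the null, 8,000 at a difference of 3.3 and 5,000 at 5.3.

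| Result | rho 0.5 | rho 0.7 | rho 0.9 |
|---|---|---|---|
| Type I error, gated test alone | 5.2% | 4.7% | 5.2% |
| Type I error, adjusted model alone | 5.3% | 4.8% | 5.1% |
| Type I error if either may count | 7.6% | 6.5% | 6.4% |
| Power at 3.3, gated v adjusted | 64.9% v 75.1% | 64.5% v 69.5% | 63.7% v 64.2% |
| Trials at 3.3 where the two disagree | 17% | 13% | 9% |
| Power at 5.3, gated v adjusted | 95.8% v 98.6% | 96.3% v 97.6% | 96.6% v 96.4% |

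The gate sent 9% to 10% of these truly normal data sets to the rank test.

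**The case against.** The strongest defence is that this is a loose sentence in a condensed article. The model is assigned to most of the data, not all. The change score is only an example, the t-test matches the sizing, and a full plan may settle which analysis leads. Part of this stands: the t-test route does agree with the sample size section, and one sentence would remove the overlap. But the article does more than leave a detail open. It fixes two methods that both cover the outcome used for sizing, and it never says that the change score is exempt from the model. If it were exempt, that outcome would lose the adjustment the paragraph defends.

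Several stronger readings are tempting and are not supported.

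- **That the plan inflates type I error.** It states no rule that either result may count. The 6.4% to 7.6% applies only if the choice is made after both are seen. The gate itself does no visible harm to the error rate with normal data.
- **That three p-values compete.** The normality check selects the t-test or the rank test, so the gated route gives one p-value and the model gives the other.
- **That the change score is biased by 0.39 SD.** That figure is the spread of the baseline imbalance, not of the bias. Over randomisation the change score is unbiased.
- **That much power is lost.** The large-sample ratio overstates the gain in arms this small, and at rho 0.9 almost nothing is gained.
- **That oxygen uptake is the one main outcome of both phases.** The article lists several primary outcomes, and the Phase II hypothesis is intramuscular. Oxygen uptake is the outcome used for sizing.

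**Conclusion.** The conflict is in the text and should be fixed, although it does not threaten the trial's validity. The main harm is that the outcome used for sizing has no single decisive analysis. For true effects well below the planned one, the two routes would often part: in about 9% to 17% of trials at 3.3 ml/kg. At the planned 5.3 ml/kg, power exceeds 95% whichever is used. The gain in precision from adjustment runs from about 22% of variance at rho 0.5 to about 1% at rho 0.9. The conditional bias of the raw change comparison has an SD of about 0.20 to 0.04 baseline SD over the same range.

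The existence of the conflict depends on reading the lost symbol as maximal oxygen uptake. Its size depends on the assumed correlation, normal data and 12 or 13 participants per arm.

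**What to change.** State that maximal oxygen uptake, and every other outcome with a baseline value, has one primary analysis: a linear model of follow-up on arm and baseline, with sex added because randomisation is stratified by it. Report the adjusted difference between arms with its 95% confidence interval. Remove Shapiro-Wilk as the selector of the test for these outcomes. Keep any t-test or rank test on raw change only as a labelled sensitivity analysis. Log-transformation of expression data and a permutation version of the model are optional.

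The cost is wording only. No measurement, visit or participant is added, since baseline and sex are already recorded. Trial status says that Phase I data collection has begun and Phase II recruitment is still to come, so the choice should be recorded with a date before any results by arm are seen.

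### The subgroup trigger correlates baseline with change from baseline, so it is driven partly by regression to the mean, and its sign is left open

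*Protocol article*

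**What the plan says.** All of the relevant text is in the Data analysis section of the protocol article. Associations are measured by Pearson correlation: "Relationships between outcome variables will be examined using a Pearson’s product-moment correlation". The rule is that "any meaningful associations (r ≥0.7) between baseline, and the magnitude of response to exercise training will be further explored by post-stratification", and the action is "post-stratification of the treatment group according to baseline status". The threshold carries no absolute-value sign and no negative bound. The section gives no cut-point for baseline status and does not say whether the correlation is computed within one arm or across both.

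Response is not defined formally, but the example the section gives for comparing arms is the "magnitude of change in absolute and relative" value of an outcome, that is, a change from baseline.

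The main analysis in the same section is a "general linear model with baseline included as a covariate, to account for any baseline imbalances because of regression to the mean".

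**The concern.** If response is follow-up minus baseline, baseline appears on both sides of the correlation. A participant whose baseline reading happens to be low will, on average, read higher next time and show a larger gain. A negative correlation between baseline and change is therefore expected from measurement error alone.

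A threshold on that correlation is a poor guide to where a real baseline-dependent response lies. Depending on how the sign is read, the rule either looks in the direction opposite to the expected pattern or selects the markers measured with least repeatability. The section recognises regression to the mean when it sets up the main model but does not carry that through to this rule. At stake is the exploratory part of the report: subgroup displays could be chosen by an artefact and read as differences in trainability.

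**Working it through.** The plan gives no figure for the behaviour of this rule, so there is none to reproduce. It is checked from first principles.

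**Inputs from the protocol.** The trigger is r ≥ 0.7 (Data analysis). Each phase recruits 32 with 15% dropout expected (Sample size estimation), in two arms (Experimental design). Assuming 1:1 allocation, 32 × 0.85 = 27.2 complete, or 16 × 0.85 = 13.6 per arm. I use n = 13 for one arm and n = 27 for both pooled.

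**Inputs assumed.** ρ is the correlation between baseline and follow-up; k is the follow-up SD divided by the baseline SD. The protocol gives neither, so ranges are shown. Data are taken as bivariate normal, with no response that depends on true baseline.

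**Expected correlation of baseline with change.**

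r = (kρ − 1) / √(1 + k² − 2kρ), which for k = 1 reduces to −√((1 − ρ)/2).

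For k = 1 this gives −0.22 at ρ = 0.9, −0.39 at 0.7, −0.50 at 0.5, −0.63 at 0.2 and −0.71 at 0. It is negative throughout. The expected value reaches −0.7 only when (1 − ρ)/2 = 0.49, so ρ = 1 − 0.98 = 0.02. For more repeatable measures, crossing 0.7 in absolute value requires sampling variation around a negative expectation.

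**A rough placing of the sample-size outcome.** The Sample size estimation section uses a "standard deviation of 3.3 ml" per kg. If that is the SD of change (not stated) and the baseline SD is between 4 and 10 (assumed), then for k = 1 the expected r is −3.3/(2 × baseline SD): −3.3/8 = −0.41 to −3.3/20 = −0.17. The corresponding ρ is 1 − 3.3²/(2 × baseline SD²): 0.66 to 0.95.

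**How often the rule fires with nothing to find** (simulation, 200,000 datasets per setting, k = 1, per marker, read as |r| ≥ 0.7):

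| ρ | n = 13 | n = 27 |
|---|---|---|
| 0.9 | 2.5% | 0.1% |
| 0.7 | 7.9% | 1.4% |
| 0.5 | 17% | 6.4% |
| 0.2 | 38% | 29% |

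Read as r ≥ +0.7, the same settings give under 0.1% at n = 13 and essentially zero at n = 27.

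**When the positive sign can occur.** The positive reading needs spread to increase. At ρ = 0.9 and k = 1.5 the expected r is (1.35 − 1)/√(1 + 2.25 − 2.7) = 0.35/√0.55 = 0.47, and r ≥ +0.7 occurs in 14% of datasets at n = 13 and about 5% at n = 27. At ρ = 0.95 and k = 1.5 it occurs in 47% and 42%.

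**What the split can show.** With k = 1 and no differential response, change falls on baseline with slope −(1 − ρ) in each arm. Splitting one arm by baseline displays that slope and offers nothing to set it against. Between randomised arms the slope is the same under the null, so a difference in slopes (the baseline-by-arm interaction) has expectation zero and is not produced by regression to the mean.

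**The case against.** The strongest reply has five parts.

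1. **The two harms belong to different readings.** If the sign is literal, noise creates almost no subgroups; if |r| is meant, the sign complaint disappears. This stands. The text does not settle which is meant, and each reading has its own defect, but they should not be added together.

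2. **For a reliable measure the problem is small.** At ρ = 0.9 the false-trigger rate is 2.5% or lower, and pooling the arms reduces it sharply. This also stands. A reader might infer that measurement error alone typically produces a correlation of 0.7. It does so only near ρ = 0. The exposure lies with poorly repeatable markers and small groups, and because the rule applies to any association, it is met marker by marker.

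3. **The literal rule is not incapable of firing.** A reader might infer that it never triggers. That holds only when spread is similar at both visits, as the k = 1.5 results show.

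4. **The sentence concerns response to training, not whether the supplement works differently by baseline.** This is a fair reading, and the interaction answers the second question. However, both arms train, so a baseline split has no untrained comparator, and the question about training response cannot be freed from regression to the mean in this way.

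5. **The action is loosely worded.** Post-stratifying the treatment group might mean comparing arms within baseline strata, which would still rest on randomisation. The criticism of an uncontrolled split therefore applies only if one arm is split. Nor does the document support talk of responder subgroups of six or seven people: no cut-point is given, and the step is described only as further exploration.

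A condensed article may leave the cut-point to a fuller document. The trigger and the action, however, are fixed here.

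**Conclusion.** The point holds in limited form. The article fixes a trigger built on two quantities that share the baseline value, leaves its sign undefined, and attaches an action that, if carried out in one arm, cannot distinguish regression to the mean from a baseline-dependent response.

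The size depends on an unstated repeatability. Under |r|, it runs from negligible (well-repeated measure, arms pooled) to more than a third of null datasets per marker (ρ = 0.2, one arm). These figures assume equal variances, normality, 1:1 allocation and 15% dropout. Under the literal sign, the rule is blind to greater gains from a low baseline and fires appreciably only if spread increases.

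A reader might go further and infer that the trial's main result is compromised. The documents do not support that: the main comparison is baseline-adjusted and the step is exploratory.

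**What to change.** Remove the r ≥ 0.7 trigger. In its place, prespecify one exploratory baseline-by-arm interaction in the planned covariate model, with baseline kept continuous and both arms included, for the primary outcome or outcomes of each phase, and report the estimate with its 95% CI. Because the intramuscular primary outcomes are a list of genes and proteins, name in advance those to which the interaction applies. Any descriptive display by baseline should compare the arms within strata, state its cut-point beforehand and be labelled exploratory.

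The cost is a sentence or two, with no change to data collection, sample size or the main analysis. The drawback is that the interaction will have low power with about 27 completers per phase, so the interval will be wide; a non-significant result should not be read as evidence that baseline does not matter.
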